| Up to first year of life | 1-2 as per early post-partum | 1-3 as per pregnancy +   1. Daily calorie target = 1,200 (+400 if breast feeding). | ≥5% weight loss from 2 months post-partum. |
| *= Cedergren, M. (2007) Optimal gestational weight gain for body mass index categories. Obstet Gynecol. 2007 Oct;110(4):759-64. | | | |

The intervention is comprised of 5 face to face interactions (60 minutes) across the antenatal and postpartum periods delivered using motivational interviewing (MI) techniques. The focus of the sessions are targeted to reflect the changing context of needs during pregnancy and the postpartum period. The intervention is supported by a facilitated ‘WhatsApp’ group, motivational text messages, a pedometer and a website. An overview of the GODDESS intervention is provided in figure 1.

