**INTERVENTION GROUP**

**Face-face MI session 1 (29-33 weeks’ gestation)**

**Given access to WhatsApp group, pedometer and website**

|  | Recruitment | Screening | Face-to-face session 1 | Face-to-face session 2 | Face-to-face session 3 | Face-to-face session 4 | Face-to-face session 5 | Interview |
| --- | --- | --- | --- | --- | --- | --- | --- | --- |
| Patient information | X |  |  |  |  |  |  |  |
| Inclusion and exclusion check | X |  |  |  |  |  |  |  |
| Patients who meet the study inclusion criteria | | | | | | | | |
| Informed consent |  | X |  |  |  |  |  |  |
| Demographics |  | X |  |  |  |  |  |  |
| Blood sample |  |  | X |  | X |  | X |  |
| Weight, height, waist circumference |  |  | X |  | X |  | X |  |
| Depression (PHQ 9) |  |  | X |  | X |  | X |  |
| Edinburgh Postnatal Depression Scale |  |  | X |  | X |  | X |  |
| Quality of life (EuroQol EQ-5D-5L) |  |  | X |  | X |  | X |  |
| Body Appreciation Scale |  |  | X |  | X |  | X |  |
| Three Factor Eating Questionnaire |  |  | X |  | X |  | X |  |
| Dietary Change Motivation Scale |  |  | X |  | X |  | X |  |
| **Risk Perception Survey for Developing Diabetes** |  |  | X |  | X |  | X |  |
| Multiple pass 24 hour diet recall (online) |  |  | X |  | X |  | X |  |
| Adapted GPAQ physical activity questionnaire |  |  | X |  | X |  | X |  |
| Sleep |  |  | X |  | X |  | X |  |
| Infant feeding intentions scale |  |  | X |  |  |  |  |  |
| Infant feeding |  |  |  |  | X |  | X |  |
| Infant data |  |  |  |  | X |  | X |  |
| Data from motion watch |  |  | X |  | X |  | X |  |
| What’sApp group and fitbit usage |  |  |  |  | X |  | X |  |
| Process evaluation |  |  |  |  |  |  |  | X |

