**X = all participants**

**X = only participants randomised to intervention group**

**2.4 Outcome Measures**

The primary outcome is feasibility of the trial. This will be assessed during the process evaluation through:

- recruitment rate
- attrition rate
- reasons for non-acceptance
- trial procedures for randomisation
- amount of staff time required
- fidelity, measured through a self-report check-list
- staff feedback on feasibility
- participants’ satisfaction with the intervention
- acceptability of research procedures, data collection and overall experience of the trial

The secondary outcomes will assess preliminary efficacy of the intervention. We will measure the following :

- Oral Glucose Tolerance Test (OGTT) to assess differences ≥1 mmol/l in either fasting or two hour postprandial glucose
- Incident T2DM and a subsequent GDM pregnancy (NICE criteria)
- Relative and absolute weight loss at multiple time points considering the number of women achieving significant weight loss (>5%) at 3 and 9 months postpartum from a baseline of the booking appointment weight
- Lifestyle factors, following the Medical Research Council (2012) diet and physical activity measurement toolkit and from accelerometer
- Other metabolic and anthropometric factors will include HbA1c, waist circumference and blood pressure
- Psychological factors; depression/anxiety (PHQ9) and postnatal depression (Edinburgh postnatal depression scale)
- Health related quality of life- EuroQol EQ-5D-5L will be used to assess health related quality of life
- Diabetes risk perception (Risk Perception Survey for Developing Diabetes used in the DPP [9]).
- Infant factors- infant feeding intentions, breast feeding duration, weight gain and growth, and measure of attachment.
- Attitudes to body [23], eating behaviour [24] and motivation for dietary change [25].
- Additional data will include: age, ethnicity, deprivation, employment, education, pre-pregnancy BMI, parity, previous GDM and birth outcome data

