### 2.4 Trial Statistics and Analysis

We do not yet have the information necessary for a formal power calculation. The aim of this study is to measure feasibility including estimating the effect size and standard deviation to formulate a power calculation for a definitive trial. The sample size of 30 in each arm would be able to detect an effect size of 0.8 in a continuous variable such as weight loss, and if allowing for a 20% attrition rate (n=16), 0.9. Therefore we do not expect do detect differences unless the effect size is large.

For the preliminary efficacy outcomes, between group and group*time interactions will be used to estimate the intervention effects (analysis of variance). The analysis will be performed using SPSS by intention to treat. Further regression analysis will be used to adjust for any potential confounding factors not factored into the stratification.

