### 3. Sample Size, Selection and Withdrawal of Subjects

A convenience sample of 60 women with current GDM, 30 in each arm will be recruited. King’s College Hospital antenatal diabetes clinic sees around 200 new patients with GDM a year, equating to 17 a month, and Guy’s and St Thomas’ Hospitals see 700 (58 a month). Participants will be recruited opportunistically at their routine clinic appointment upon diagnosis of GDM, group education session the following week, or at a following clinic visit, by a diabetes nurse, consultant or dietician. We estimate that with a 30% recruitment rate we can recruit our sample within 3 months, or with a 15% recruitment rate we can recruit within 6 months. The intervention will last approximately 12 months (depending on gestational stage at diagnosis – usually this is around 28 weeks but can be earlier), with follow-up stopping at 9 months postpartum. We aim to start recruitment, ethical approval permitting, in March 2018, and finish data collection in September 2019. We expect the data to be analysed by December 2019.

Pregnant women have been chosen because: (1) previous research and our qualitative research indicates this is the best time to recruit women to start providing support, (2) women are already engaged with health services so may be easier to recruit, (3) women may be more receptive to behaviour change support during pregnancy, and (4) the highest cumulative incidence of T2DM after GDM is in the first 5 years postpartum, so any intervention should start as soon as possible after identification of GDM.

Potential participants will be identified by the clinical team working at KCH and GSTT. Potential participants will be given the participant information sheet explaining the purpose of the study. Participants who indicate a potential interest in the study will be given the opportunity to consider their participation in the study before being scanned by the researcher for full eligibility using the eligibility screening form. After screening, if the patient is eligible they will undergo consenting, either on the same day or another day at their convenience. Participants may withdraw their interest in the study at any point during the screening and consenting process and their details will not be stored.

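### Breast feeding duration falls under the single ANOVA method, but some durations will be incomplete at last contact, so its result depends on a handling choice the protocol does not state

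*Protocol*

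**What the plan says.** Protocol section 2.4 (Outcome Measures) includes "Infant factors- infant feeding intentions, breast feeding duration, weight gain and growth, and measure of attachment" in its secondary list and gives that list its purpose: "The secondary outcomes will assess preliminary efficacy of the intervention".

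The statistics section, also numbered 2.4, names one approach for the preliminary efficacy outcomes: "between group and group*time interactions will be used to estimate the intervention effects (analysis of variance"). It adds: "The analysis will be performed using SPSS by intention to treat". Durations are not treated separately.

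The rest of the protocol determines what can be observed:

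- The visit schedule (2.3) and the data collection lists (4.2) record infant feeding at 3 and 9 months postpartum only.
- Section 3 describes the intervention period "with follow-up stopping at 9 months postpartum".
- Section 4.1 says that no further data are collected after withdrawal. Section 3.3 withdraws women who become pregnant again or are diagnosed with diabetes.
- The statistics section makes a planning allowance for loss: "if allowing for a 20% attrition rate (n=16), 0.9".

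**The concern.** A woman who is still breast feeding when last seen has no completed duration, only the statement that it exceeds a known time. The protocol's own design can create two such groups: women still feeding at the 9-month visit, and women lost earlier while still feeding. ANOVA needs one number per woman, so someone must decide whether to leave these women out or to enter the time at last contact as if it were the duration. The protocol gives no rule.

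Duration is also one value per woman with no baseline, so only the between-group half of the stated method can apply to it.

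The incomplete values need not be balanced between arms. Breast feeding is an early postpartum target in Table 1 of section 2.2, and session 1 materials cover it. If the programme prolongs feeding, more intervention women will be incomplete. At stake are the effect size and SD reported for this outcome. The statistics section says that estimating these quantities for a definitive trial is part of the study's aim.

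**Working it through.** The protocol states no figure for feeding duration, so there is none to reproduce. It also gives no feeding rates. What follows is a sensitivity calculation under assumptions.

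**Inputs from the protocol.** 30 women per arm; end of follow-up at 9 months; feeding recorded at 3 and 9 months; a 20% attrition allowance, which leaves 30 × 0.8 = 24 per arm.

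**Assumptions.** Exponential durations; a proportion p of 15%, 30% or 45% of control women still feeding at 9 months; a stopping hazard ratio of 0.67; dropouts last seen at 3 months and lost independently of feeding.

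**Formulas.**

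- Control rate: a = −ln(p)/9. Intervention rate: b = 0.67a. Intervention proportion still feeding at 9 months: p^0.67.
- Mean feeding time to t months: R(t) = (1 − e^(−rate × t))/rate.
- Mean among women who stopped before 9 months: (R(9) − 9p)/(1 − p), with each arm's own p.
- Mean with a fraction d of the arm scored at 3 months if still feeding then: (1 − d)R(9) + d·R(3).

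**Worked case, p = 15%.**

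- a = 1.897/9 = 0.2108 and b = 0.1412. The intervention proportion still feeding is 28%.
- R(9) = 0.85/0.2108 = 4.03 (control) and 0.719/0.1412 = 5.09 (intervention). Difference: 1.06 months.
- Ongoing feeders excluded: (4.03 − 1.35)/0.85 = 3.16 and (5.09 − 2.52)/0.719 = 3.57. Difference: 0.42 months, or 39% of 1.06.
- R(3) = 2.22 and 2.45. With 20% lost in each arm: 0.8 × 1.06 + 0.2 × 0.22 = 0.89 months, which is 16% too small.
- With 30% lost in control and 10% in intervention: (0.9 × 5.09 + 0.1 × 2.45) − (0.7 × 4.03 + 0.3 × 2.22) = 1.34 months, which is too large.

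**All three cases** (differences in months, intervention minus control):

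| | p = 15% | p = 30% | p = 45% |
|---|---|---|---|
| Still feeding at 9 months, of 24 (control / intervention) | 4 / 7 | 7 / 11 | 11 / 14 |
| Mean feeding time to 9 months | 1.06 | 0.94 | 0.77 |
| Completers scored at 9 months, no dropout | 1.06 | 0.94 | 0.77 |
| Ongoing feeders excluded | 0.42 (39%) | 0.28 (30%) | 0.19 (25%) |
| Dropouts at last contact, 20% in each arm | 0.89 | 0.79 | 0.64 |
| Dropouts at last contact, 30% control, 10% intervention | 1.34 | 1.42 | 1.42 |
| Total duration, 1/b − 1/a | 2.3 | 3.7 | 5.6 |

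With equal dropout, last-contact scoring falls short by 0.13 to 0.17 months, or 16% to 17%. With a hazard ratio of 0.5, exclusion keeps 24% to 36% of the 9-month difference, so the pattern does not hinge on 0.67.

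The second and third rows of differences agree by construction. Entering 9 for a completer who is still feeding gives the mean of the shorter of her duration and 9 months, which is the restricted mean itself. The last row shows why the outcome needs a stated horizon: total duration, which the unqualified wording could mean, is a much larger difference that this follow-up cannot observe.

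**The case against.** The analysis sentence is a generic summary over mixed outcomes, and detailed handling of one infant item is ordinary analysis-plan content. That has weight, and the absence of a plan is not the complaint. The complaint is that the protocol names a method for this class of outcomes and the method does not suit this one.

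The between-group term is listed separately and can be applied to a duration. That stands; only the group-by-time part is empty.

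A reader might infer that the trial will lose most of the effect, as in the exclusion row. The protocol does not support that. It never says that ongoing feeders are deleted, it specifies intention to treat, and it keeps data already collected. If completers are scored at 9 months, only the dropouts remain a problem. With equal dropout the resulting bias is 0.13 to 0.17 months, against a standard error of about 0.9 months with 24 per arm (SDs of roughly 3 months in the worked cases).

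A reader might also infer that the arm difference must shrink. That needs roughly equal dropout; the 30%/10% row reverses it. Nor does the protocol forecast 20% loss: the figure is an allowance.

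Finally, Table 1's row for the period up to the first year contains "Daily calorie target = 1,200 (+400 if breast feeding"). It might be read as foreseeing feeding past 9 months. The row follows the 0 to 3 month row and could apply at any time from month 3, so it does not settle the matter.

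**Conclusion.** The point holds as a minor one. ANOVA as named does not suit a single-value outcome that can be incomplete at last contact, and the result then depends on a choice the protocol does not make. Under the stated assumptions, the estimated 9-month difference ranges from 25% to 39% of its true value (ongoing feeders excluded), through no bias (completers scored at 9 months), to about 16% too small (dropouts at last contact, equal loss) or too large (control loss of 30% against 10%). Neither the direction nor the size is fixed by the documents: feeding rates, the shape of the distribution, the hazard ratio and the dropout pattern are all assumed.

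The effect is confined to the effect size and SD reported for this one secondary outcome. The feasibility conclusion is untouched, and nothing in the protocol says that feeding duration will size the definitive trial; its own sizing example is weight loss.

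**What to change.** In section 2.4:

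- Rename the outcome *breast feeding duration up to 9 months* and take it out of the ANOVA.
- Ensure that the infant feeding item at 3 and 9 months records whether the woman still breast feeds and, if not, the infant's age at stopping. The item's questions are not shown, so it may already do this.
- Count women who never start as 0. Censor women lost while still feeding at their last contact.
- Report Kaplan-Meier curves by arm, the difference in restricted mean feeding time to 9 months with a 95% CI, and the proportions feeding at 3 and 9 months.
- State that censoring assumes loss unrelated to feeding, which is doubtful where a new pregnancy leads to withdrawal under section 3.3.

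The cost is a few sentences and at most one question within an item already scheduled, with no extra visits or participants. It should be settled before the 3-month visits, because stopping ages are hard to recover later. The downside is that the outcome no longer claims total duration.

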**Figure 1. CONSORT flowchart**

**29-32 weeks' gestation:** Dietician or researcher provide information to potentially eligible participant during group education session. Or clinician providing routine care to approach potentially eligible participants at first clinic appointment - brief verbal and written information given and verbal permission for researcher to contact sought

**Baseline / randomisation visit (29-33 weeks' gestation):** Eligibility confirmed; written informed consent (if not previously obtained); randomisation; demography; questionnaires; anthropometry; blood pressure; blood sample; OGTT, provided with 7 day accelerometer and instructions

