**4.4 Schedule of Treatment for each visit**

Data from consenting patients who meet the inclusion criteria and are randomised to the intervention group will receive the following treatment.

| **Table 1: Face-to-face motivational interviewing (MI) Sessions** |
| --- |
| **Session 1: Diagnosis - 2 weeks post diagnosis of GDM (60 mins)** |
| Focus:   - Allow patient to ventilate and express their thoughts and feelings about the diagnosis and their concerns and health beliefs. - Elicit patient’s understanding of diabetes risk and provide simple explanation- confirm understanding. - Elicit what the patient thinks will reduce their risk and provide menu of potential actions that may reduce risk- explore pros and cons with patient. - Encourage patient to choose areas of action, focus on discrete behaviours such as: consumption of sugary drinks, snacks, fast-food, portion sizes and increasing walking. - Explore importance and confidence of action areas- develop self-efficacy as required. - Set pregnancy lifestyle goals (diet and physical activity) with patient using SMART model. - Get patient to identify what personal and social resources they will use in achieving goals. - Introduce and fit patient with the wearable technology (pedometer). - Introduce participant to WhatsApp group   Materials:   - Prompt-card detailing factors contributing to their risk of diabetes. - Prompt-card benefits to their health in pregnancy and for their baby. - Prompt-card with menu of lifestyle steps they can take in pregnancy. - Credit-card sized summary with key messages and web address for additional support. - Pros and cons of breast feeding in terms of diabetes risk for patient and baby.   Targets:   - Patient understands diabetes risk and contributing factors. - Patient motivation and activation. - Patient identifies diet and activity goals. - Patient is familiar with can use pedometer. - Patient is familiar with and can access WhatsApp group. |
| **Session 2:Third trimester (60 minutes)** |

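### Infant feeding intentions are listed as an efficacy outcome but measured only once, at the baseline visit, with no safe order relative to randomisation and session 1

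*Protocol*

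**What the plan says.** **Status of the variable.** Protocol section 2.4 (Outcome Measures) states: "The secondary outcomes will assess preliminary efficacy of the intervention". One bullet in the list that follows begins "Infant factors- infant feeding intentions, breast feeding duration" and goes on to infant growth and attachment. Descriptive variables have a bullet of their own at the end of the list: "Additional data will include: age, ethnicity, deprivation, employment, education, pre-pregnancy BMI, parity, previous GDM and birth outcome data". Feeding intentions are not in that last bullet.

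**When it is measured.** In the schedule table of section 2.3, the row "Infant feeding intentions scale" has a single mark, in the column for face-to-face session 1. Section 4.2 lists the scale under data collection visit 1, which it introduces as baseline data. Visits 2 and 3 (3 and 9 months postpartum) have an infant feeding item instead.

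**Order at the baseline visit.** The flowchart (Figure 1, section 2.3) gives this sequence: "written informed consent (if not previously obtained); randomisation; demography; questionnaires; anthropometry". The session 1 materials in section 4.4 include "Pros and cons of breast feeding in terms of diabetes risk for patient and baby".

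**Analysis.** For the preliminary efficacy outcomes, section 2.4 (Trial Statistics and Analysis) says that "between group and group*time interactions will be used to estimate the intervention effects (analysis of variance"). It then adds regression to adjust for possible confounders and names no covariates.

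**The concern.** An efficacy outcome needs a value that treatment could have changed. As scheduled, this one has either no such value or an ambiguous one. Two things are at stake.

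First, a chance difference between arms in feeding intention could be reported alongside real post-treatment outcomes, such as breast-feeding duration and infant growth, as if it were an effect of the intervention.

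Second, the score has a good use that the present wording puts at risk. Breast feeding is a behavioural target in the early postpartum period (Table 1, section 2.2) and its duration is an outcome. Duration for this infant cannot have a baseline value of its own, and feeding intention is the one collected baseline measure specific to it. It can serve as a covariate only if neither allocation nor session 1 can have influenced it, and the protocol does not fix that.

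**Working it through.** **1. Can the planned effect be estimated?** The group-by-time effect is (later mean − baseline mean) in the intervention arm minus the same change in the control arm. With one measurement occasion there is no later mean in either arm, so the term does not exist. Only a between-arm contrast at that one occasion remains.

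**2. What would that contrast mean?** It depends on when the scale is completed.

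| Scale completed | Meaning of an arm difference | Safe as baseline covariate? |
|---|---|---|
| Before randomisation | Chance imbalance only | Yes |
| After allocation is known, before session 1 | Chance plus any reaction to allocation | No |
| After session 1 (intervention arm) | Chance plus any effect of session 1 | No |

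For the first row, with 30 women per arm (section 3), the standard error of the difference is √(2/30) = 0.258 SD of the score. Chance alone then gives differences of up to 1.96 × 0.258 = 0.51 SD in 95% of such trials.

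**3. Which row applies?** Section 4.2 calls the data baseline, which points to the first row. The flowchart names randomisation before questionnaires within the same visit, which points to the second. The schedule table places the scale in the session 1 column, and both the baseline visit and session 1 fall at 29–33 weeks' gestation, which leaves the third open. Nothing in the protocol decides between them.

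**4. Why the order matters for adjustment.** The adjusted arm difference in a breast-feeding outcome is the raw difference minus b × (difference in mean intention score), where b is the within-arm slope. If the score precedes randomisation, this subtraction removes chance imbalance. If the score has already moved because of allocation or session 1, it subtracts part of the intervention's own effect.

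**5. Size of the precision gain.** The protocol's only effect-size figures concern a continuous variable such as weight loss: 0.8 with 30 per arm, and 0.9 after 20% attrition. It states neither alpha nor power. With a two-sided 5% t-test assumed, 0.8 with 30 per arm has power 0.861. No figure is given for any breast-feeding outcome, so nothing there carries over.

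For a continuous outcome, adjusting for a baseline score with correlation ρ multiplies the standard error by √(1 − ρ²). The protocol gives no ρ, so the values below are assumptions. The arm size of 24 is 60 × 0.8 / 2. The unadjusted 95% half-width is 1.96 × √(2/24) = 0.57 SD.

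| ρ (assumed) | √(1 − ρ²) | Reduction in SE | 95% half-width, 24 per arm |
|---|---|---|---|
| 0 | 1.000 | 0% | 0.57 SD |
| 0.3 | √0.91 = 0.954 | 4.6% | 0.54 SD |
| 0.5 | √0.75 = 0.866 | 13.4% | 0.49 SD |
| 0.6 | √0.64 = 0.800 | 20.0% | 0.45 SD |

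The cost is one residual degree of freedom (48 − 2 = 46 becomes 48 − 3 = 45). The formula assumes a fully observed continuous outcome. Follow-up stops at 9 months postpartum, so duration is censored for women still feeding, and the table is only a guide.

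**The case against.** The best defence is that this is a labelling slip. The list in section 2.4 also carries age, ethnicity and parity, so it is not purely a list of endpoints, and section 4.2 plainly calls the visit 1 data baseline. The schedule's columns carry session names although control women attend no sessions, so the session 1 column may simply mean the baseline visit. Much of this is fair, and it is why the point is minor. It does not remove the point: the descriptive variables have a separate bullet, the intentions score sits with genuine outcomes, and the order relative to randomisation stays open.

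Three stronger readings are tempting, and the documents do not support them.

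- *An arm comparison of intentions is meaningless.* That holds only if the scale precedes allocation. If it follows allocation or session 1, the comparison has some meaning, but the score is then not a baseline.
- *The breast-feeding comparison is left without adjustment.* The planned regression names no covariates and excludes none. A chance imbalance in a predictor of duration could well be covered by its wording, and the choice of covariates is commonly left to a statistical analysis plan, which is not at hand. The between-arm part of the planned analysis can also apply to duration, which is a single value per woman.
- *A definite amount of power is lost.* Any such figure would borrow an effect size given for a variable such as weight loss and add an assumed correlation. The protocol says it lacks the information for a formal power calculation and does not expect to detect differences unless the effect is large.

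**Conclusion.** The point holds as an inconsistency within the protocol. Infant feeding intentions are classed as a preliminary-efficacy outcome, yet the schedule gives them one measurement, with the baseline data, so the planned group-by-time effect cannot be estimated. If that measurement precedes allocation, a difference between arms is chance and not an effect. As written, it could also follow allocation or session 1, which would make the score unsafe as a baseline. No analysis plan could supply the missing later measurement.

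Using the score as a covariate for breast-feeding outcomes is a recommendation, not the repair of a proven omission. Its benefit is a standard error about 5% to 20% smaller for correlations of 0.3 to 0.6, all assumed, and no power figure should be quoted as the protocol's own. Severity is minor: the primary outcome is feasibility and no main conclusion depends on this item.

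**What to change.** 1. In section 2.4 (Outcome Measures), move infant feeding intentions out of the efficacy outcomes and list the scale with the baseline data.
2. In the flowchart and schedule table of section 2.3, and in the visit 1 list of section 4.2, state that the scale is completed before randomisation and before session 1.
3. In section 2.4 (Trial Statistics and Analysis), state that breast-feeding outcomes, which have no baseline of their own, are compared between arms with the baseline intention score as a prespecified covariate. For duration, use a model that allows for censoring at 9 months.

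The cost is changes of wording, a fixed order of tasks at the baseline visit and one degree of freedom. No new data are needed.
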